# Interventions to de-implement unnecessary antibiotic prescribing for ear infections (DISAPEAR Trial): protocol for a cluster-randomized trial

**DOI:** 10.1186/s12879-023-08960-z

**Published:** 2024-01-24

**Keywords:** Acute otitis media, Antibiotic stewardship, Implementation effectiveness, Watchful waiting

## Abstract

**Background:**

Watchful waiting management for acute otitis media (AOM), where an antibiotic is used only if the child’s symptoms worsen or do not improve over the subsequent 2–3 days, is an effective approach to reduce antibiotic exposure for children with AOM. However, studies to compare the effectiveness of interventions to promote watchful waiting are lacking. The objective of this study is to compare the effectiveness and implementation outcomes of two pragmatic, patient-centered interventions designed to facilitate use of watchful waiting in clinical practice.

**Methods:**

This will be a cluster-randomized trial utilizing a hybrid implementation-effectiveness design. Thirty-three primary care or urgent care clinics will be randomized to one of two interventions: a health systems-level intervention alone or a health systems-level intervention combined with use of a shared decision-making aid. The health systems-level intervention will include engagement of a clinician champion at each clinic, changes to electronic health record antibiotic orders to facilitate delayed antibiotic prescriptions as part of a watchful waiting strategy, quarterly feedback reports detailing clinicians’ use of watchful waiting individually and compared with peers, and virtual learning sessions for clinicians. The hybrid intervention will include the health systems-level intervention plus a shared decision-making aid designed to inform decision-making between parents and clinicians with best available evidence. The primary outcomes will be whether an antibiotic was ultimately taken by the child and parent satisfaction with their child’s care. We will explore the differences in implementation effectiveness by patient population served, clinic type, clinical setting, and organization. The fidelity, acceptability, and perceived appropriateness of the interventions among different clinician types, patient populations, and clinical settings will be compared. We will also conduct formative qualitative interviews and surveys with clinicians and administrators, focus groups and surveys of parents of patients with AOM, and engagement of two stakeholder advisory councils to further inform the interventions.

**Discussion:**

This study will compare the effectiveness of two pragmatic interventions to promote use of watchful waiting for children with AOM to reduce antibiotic exposure and increase parent satisfaction, thus informing national antibiotic stewardship policy development.

**Clinical trial registration:**

NCT06034080.

**Supplementary Information:**

The online version contains supplementary material available at 10.1186/s12879-023-08960-z.

## Background

Acute otitis media (AOM) is the most common reason children are prescribed antibiotics, affecting 5 million children and resulting in 10 million antibiotic prescriptions annually [1–3]. Though 84% of AOM episodes resolve without antibiotics [4, 5], antibiotics are prescribed to approximately 95% of children when AOM is diagnosed, [6, 7]. The use of unnecessary antibiotics contributes to the development of antibiotic-resistant organisms, making future infections more difficult to treat [8]. In fact, recent data indicates that antibiotic resistance is rapidly increasing among bacteria that commonly cause AOM [9]. Antibiotics also place children at risk for *C. difficile* infection [10], are associated with an increased risk for chronic diseases later in life [11–13], and reduce pediatric quality of life. More than a quarter of children receiving an antibiotic will experience an adverse drug event [14]. One way to reduce unnecessary antibiotic exposure is to use a watchful waiting approach for the treatment of AOM, where an antibiotic is started only if the child’s symptoms worsen or do not improve over the subsequent 2 to 3 days [15]. A watchful waiting approach may include: (1) observation, where symptoms are monitored and an antibiotic is prescribed at a later date if symptoms worsen or do not improve, or (2) a delayed antibiotic prescription, where an antibiotic is prescribed during the initial encounter, but parents are instructed to start the antibiotic only if symptoms worsen or do not improve. In previous clinical trials of children with AOM or other respiratory infections, watchful waiting was shown to reduce antibiotic use by over 62% and did not result in worsening of symptoms, a higher rate of complications, or reduced parent satisfaction [16–22]. Despite the results of these trials, fewer than 5% of children with AOM are managed with watchful waiting in clinical practice [7, 23–25].

The infrequent use of watchful waiting to manage AOM may be associated with barriers such as a lack of institutional guidance or clinical workflows to support this approach, concerns about the time and feasibility to communicate with families after the initial visit, and potential co-pays for additional visits. Furthermore, clinicians may prescribe an immediate antibiotic over watchful waiting because they believe parents expect an antibiotic; however, this is often an incorrect assumption [26, 27]. While most parents do believe an antibiotic is required to treat AOM, they also consistently report that pain management, not an antibiotic, is the most important aspect of their child’s AOM care [28]. As such, ensuring effective communication and discussion of treatment options between parents and clinicians during AOM management may improve care and reduce unnecessary antibiotic use.

One such method for promoting engagement between parents and clinicians is through shared decision-making [2]. Shared decision-making is an approach whereby parents and clinicians come to mutual agreement upon a treatment strategy when there is uncertainty about the most effective treatment approach or differing opinions about the optimal treatment. Shared decision-making is typically facilitated with the use of a conversation aid designed to inform the decision-making between parents and clinicians with best available evidence. A prior study of shared decision-making for AOM found that its use resulted in a 20% absolute reduction in antibiotic use and a 17% absolute increase in parent satisfaction [29]. While shared decision-making interventions may be effective tools to facilitate watchful waiting management, they have not been successfully scaled to improve care for children with AOM. Like shared decision-making interventions, health systems-level interventions have also led to reductions in prescribing for AOM; [23, 24, 30] however, studies comparing the effectiveness of health systems-level interventions and shared decision-making, or their use in combination, are lacking. Such studies are essential to develop appropriate guidance on the most effective approaches to minimize antibiotic exposure for children with AOM. The present study will compare the effectiveness and implementation outcomes of two pragmatic, patient-centered interventions to promote use of watchful waiting: a health systems-level intervention alone or a health systems-level intervention combined with shared decision-making. Both intervention approaches aim to reduce antibiotic exposure for children with AOM while increasing parent engagement and satisfaction with their child’s care.

## Methods

### Overview of study design

 This will be a pragmatic, cluster-randomized controlled trial that will use a hybrid implementation-effectiveness design [31]. The effectiveness and implementation outcomes of a “gold standard” [32] health systems-level intervention and a hybrid health systems-level plus shared decision-making intervention will be compared using the Practical Robust Implementation and Sustainability Model (PRISM) [33] and Reach Effectiveness Adoption Implementation Maintenance (RE-AIM) frameworks [34]. Participating clinics will be randomly assigned to one of the two interventions (Fig. 1) using covariate-constrained randomization. The primary outcomes of the study are 1) parent satisfaction with their child’s treatment for AOM, and 2) antibiotic courses *taken* by children with AOM by parent report. Secondary outcomes include 1) shared decision-making process and effectiveness [35, 36], 2) pediatric quality of life [14], 3) symptom severity and duration [22, 37, 38], 4) missed work, school, and daycare, 5) adverse drug events [14], 6) treatment failure [25, 39], 7) management strategy used (immediate antibiotic versus watchful waiting), and 8) whether or not an antibiotic prescription was filled at a pharmacy (Table 1).

**Fig. 1 Fig1:**
[figure not shown]
Cluster-randomized trial design

**Table 1 Tab1:** Primary and secondary outcome measures

Outcome	Metric^a^	Data Source	Time of Measurement(s) (Days)
Co-primary outcomes			
Antibiotic Taken	% filled and took antibiotic (yes/no)	Survey	10
Parent Satisfaction	% very or extremely satisfied- Likert scale (7- point) Validated	Survey	10
Secondary outcomes			
Shared decision-making (Process measure)	Summed Score- Knowledge and Decisional Conflict Assessment. Shared Decision-Making Questionnaire (SDM-Q-9)	Survey	0
Pediatric Quality of Life	PEDS-QL Score	Survey	10
Symptom Severity and Duration	Likert scale (7-point) Validated [22, 37]- all ages AOM-Severity of Symptom scale [38]- age 6–35 months	Survey	0, 10
1. Symptom severity (max and day 10)	Above	Survey	0, 10
2. Time to symptom improvement	Above	Survey	0, 10
3. Time to all symptom resolution	Above	Survey	0, 10
4. Time to ear pain resolution	Above	Survey	0, 10
5. Symptoms resolved at day 10	Above	Survey	10
Missed Work, School, Daycare	# Days missed school/daycare # Days parents missed work	Survey	10
Adverse Drug Events	% with adverse drug event(s)	Survey	10
Treatment Failure	% changed management (took antibiotic if initially watchful waiting or new antibiotic if initially immediate antibiotic)	Survey and EHR^b^	10
Management Strategy Used (Process Measure)	% immediate antibiotic	EHR	0
Antibiotic Filled (Process Measure)	% filled antibiotic (even if not taken)	Survey	10

^a^A comparable tool or measure may be substituted

^b^*EHR* Electronic health record

### Study setting and population

A total of 33 clinics from three geographically disparate health systems – AllianceChicago (AC) (a network of community health centers in Chicago, IL, USA), Denver Health and Hospital Authority (DHHA) (Denver, CO, USA), and Intermountain Health (IH) (Salt Lake City, UT, USA) – will be randomized. The participating clinics include over 200 pediatric, family medicine, and urgent care clinicians who serve more than 6,000 children with AOM annually (Table 2). The participating sites were selected to represent a diverse population that includes children of different races, ethnicities, language preferences, and socioeconomic statuses. Because most antibiotics for children in the United States are prescribed in non-academic settings, all participating clinics are community-based to increase the generalizability of study findings [21, 40].

**Table 2 Tab2:** Aggregate data of clinic and patient characteristics for each participating site

**Clinic Characteristics**	**Alliance Chicago N (%)**	**Denver Health and Hospital Authority N (%)**	**Intermountain Healthcare N (%)**
Clinics to be randomized	10	9	14
Total eligible clinics	45	33	31
Family Medicine	0	7	0
Pediatric	0	23	0
Urgent Care	0	3	31
Hybrid (multi-specialty)	45	0	0
Clinical setting (participating)			
Urban	TBD	9 (100)	3 (10)
Suburban	TBD	0 (0)	24 (77)
Rural	TBD	0 (0)	4 (13)
Clinicians per clinic (mean eligible clinicians, range)	20.3 (3–51)	22.1(10–38)	29.3 (2–60)
Clinician Type			
Physician	TBD	123 (61.8)	205 (71.9)
Advanced Practice Provider	TBD	43(21.6)	80 (28.1)
Annual acute otitis media encounters per clinic (mean, range)	382 (121–1172)	228 (40–468)	346 (2–944)
**Patient Demographics**^a^	**N (%)** ***N***** = 12,449**	**N (%)** ***N***** = 7,524**	**N (%)** ***N***** = 12,818**
Age (mean ± standard deviation, years)	4.3 (± 3.9)	3.4 (± 3.1)	5.2 (± 4.5)
Race			
American Indian/Alaskan Native	50 (0.4)	60 (0.8%)	91 (0.7%)
Asian	336 (2.7)	278 (3.7%)	152 (1.2%)
Black/African American	2042 (16.4)	1091 (14.5%)	163 (1.3%)
Native Hawaiian/Pacific Islander	212 (1.7)	45 (0.6%)	266 (2.1%)
White	7718 (62.0)	5477 (72.8%)	11,695 (91.2%)
Other/Unknown	2104 (16.9)	579 (7.7%)	451 (3.5%)
Ethnicity			
Hispanic/Latinx	7656 (61.5)	5116 (68.0%)	1,939 (15.1%)
Non-Hispanic/Latinx	4431 (35.6)	2408 (32.0%)	10,644 (83.1%)
Declined/Unknown			234 (1.8%)
Language Preference			
English	7108 (57.1)	4703 (62.5%)	12,556 (98.0%)
Spanish	5041 (40.5)	2332 (31.0%)	225 (1.8%)
Other	286 (2.3)	489 (6.5%)	37 (0.3)
Insurance			
Public (Medicaid, etc.)	9275 (74.5)	6629 (88.1%)	2406 (18.8%)
Commercial	3175 (25.5)	707 (9.4%)	9751 (76.1)
Uninsured	0 (0)	68 (0.9%)	661 (5.2%)
Unknown	0 (0)	120 (1.6%)	0 (0)

### Formative evaluation of context with PRISM

PRISM will be used to guide the formative implementation evaluation of the interventions. PRISM has demonstrated efficacy in identifying contextual factors to facilitate intervention adaptations to prevent program failure and increase program uptake across diverse settings. Assessment of external and internal factors using the PRISM domains of 1) Organizational Perspective, 2) Patient Perspective, 3) External Environment, 4) Implementation and Sustainability Infrastructure, 5) Organizational Characteristics, and 6) Patient Characteristics will be conducted using a mixed methods approach in the pre-implementation phase to make necessary program adaptions and guide implementation strategies (Table 3).

**Table 3 Tab3:** Practical robust implementation and sustainability model (PRISM) components

PRISM domain	What are we assessing?	How will data be collected?	How will data be used?
Organizational perspective	• Preferred mechanisms to relay program changes and education to clinicians • Baseline antibiotic prescribing patterns for AOM • Contextual factors that may facilitate/impede watchful waiting • Contextual factors that may facilitate/impede implementation of intervention components	• Key informant interviews (clinicians and administrators) • Process mapping interviews (clinicians and administrators) • Electronic health record (EHR) data	• Adapt implementation plan to meet local needs and address barriers • Feedback baseline data to clinicians
Patient perspective	• Receptiveness to use of watchful waiting for AOM • Contextual factors that may facilitate/impede the acceptance of watchful waiting • Parent preferences for SDM process	• Key informant focus groups (parents)	• Adapt SDM process and education for clinicians to meet parent needs (Hybrid only) • Adapt communication education for clinicians • Adapt patient education materials
External environment	• HEDIS^a^ measures for antibiotic prescribing for acute respiratory tract infections • Cosmopolitanism	• Key informant interviews (clinicians and administrators) • EHR data to compute HEDIS measure	• Incorporate into clinician education and use for administrative buy-in if needed
Implementation and sustainability infrastructure	• Current resources and resource utilization for AOM management (e.g., EHR-tools, education materials) and stewardship • Baseline workflow for AOM • Perceived facilitators/barriers to sustainability	• Key informant interviews (clinicians and administrators) • Process mapping interviews (clinicians and administrators)	• Adapt sustainability plan and EHR workflow • Develop workflow for SDM (Hybrid only)
Organizational characteristics	• Existing collaborations and information flow between clinics • Administrative support • Shared goals	• Key informant interviews (clinicians and administrators)	• Modify communication plan and add administrative support if needed
Patient characteristics	• Demographics • Urban, suburban, rural designation	• EHR data collection • Clinic zip codes	• Use data for covariate-constrained cluster randomization

^a^
*HEDIS* Healthcare effectiveness data and information set

Contextual factors will be assessed at the child/parent, clinician, clinic, and health systems-levels using key informant semi-structured interviews and focus groups, process mapping, and electronic health record (EHR) data. Semi-structured key informant interviews will be conducted with a convenience sample of clinic administrators and clinicians across participating clinics to understand 1) typical workflow of visits for children with AOM, 2) contextual factors that may facilitate or impede use of watchful waiting, 3) contextual factors that may facilitate or impede implementation of intervention components, and 4) organization culture. To understand parent perspectives of factors that may facilitate or impede the acceptance of watchful waiting, focus groups of a convenience sample of parents from each site will be conducted.

Finally, to better understand variability in care, assist with setting targets for improvement, and inform the randomization of clinics, baseline EHR data will be abstracted to evaluate pre-intervention antibiotic prescribing patterns and patient-level characteristics from potential participating clinics. Substantial efforts will be made to minimize missing data on predictors by abstracting data from multiple EHR locations. For missingness of key predictors, sensitivity analyses will be carried out using multiple imputation approaches [41].

### Intervention components

The components of the health systems-level intervention are based on the CDC Core Elements of Outpatient Antibiotic Stewardship and broadly include engagement of a clinician champion at each participating clinic, changes to electronic health record to facilitate use of delayed antibiotic prescriptions, quarterly feedback reports detailing clinicians’ use of watchful waiting with comparison to their peers, and virtual learning sessions for clinicians [32]. The hybrid intervention will include the same elements as the health systems-level intervention with the addition of a shared decision-making aid and education sessions for clinicians regarding use of the aid. The interventions will be adapted based on the formative evaluation. A national stakeholder group comprised of representatives from the American Academy of Pediatrics (AAP), Centers for Disease Control and Prevention (CDC), and Pew Charitable Trusts provided input into the development of this work and will be convened at regular intervals over the study period to ensure that the interventions are low-cost, feasible to implement, generalizable, and sustainable.

### Clinician champions

Each participating clinic will be assigned a clinician champion to serve as the liaison for the study. The clinician champions will promote and advocate use of the assigned intervention tools as well as provide support and education for their peer clinicians throughout the intervention period.

### EHR tools

The participating clinics utilize three distinct EHRs – Epic, Cerner, and Athena. Together, these three EHRs account for over 75% of the EHR market in the United States. EHR changes will include updates to prescription fields to enable clinicians to more easily order a delayed antibiotic prescription as part of a watchful waiting approach to treatment. Patient education materials with watchful waiting instructions will be added to the EHR in languages appropriate for the patient populations (English, Spanish) at a fifth-eighth grade or below literacy level so that clinicians can include them in the after-visit summary. The information contained in the English and Spanish versions of the materials will be identical. Clinics will also have direct access to printable materials to accommodate their preferred method of dissemination.

### Audit and feedback reports for clinicians

Quarterly feedback reports detailing participating clinicians’ use of watchful waiting individually and compared with their peers will be created and shared using the Outpatient Automated Stewardship Information System (OASIS^©^). OASIS^©^ is a free, open-source method that uses statistical software to automate audit and feedback report creation and distribution and track clinician review of reports. The reports will show each clinician’s use of watchful waiting (observation or delayed antibiotic prescription vs immediate prescription) for AOM in children ≥ 6 months old in comparison to the same metric for peers in their clinic.

### Clinician education

Clinician education will include two optional one-hour virtual learning sessions. Education will focus on the clinical course of pediatric AOM with and without antibiotics, risks associated with antibiotics, and communication using the Dialogue Around Respiratory Treatment (DART) curriculum [42]. Learning sessions will be recorded. Continuing medical education (CME) and/or Maintenance of Certification (MOC) credit will be provided to participating clinicians. Clinicians who practice in clinics randomized to the hybrid health systems-level plus shared decision-making intervention will also receive access to an electronic or paper shared decision-making aid to use during AOM visits, along with education about use of the aid.

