### Statistical analysis

The co-primary outcomes – whether the antibiotic was filled and taken and whether the parent was ‘very’ or ‘extremely satisfied’ with their child’s care – will be analyzed with a logistic mixed effects regression model. This model accounts for the hierarchical structure of the data with patients nested within clinics. The primary analysis will include covariates for the intervention group, the random effect for clinic, and pre-specified confounding factors including age, race, gender, ethnicity, language preference, and insurance type. Any variables that appear unbalanced between the study arms at *p* < 0.2 will also be included as predictors. Since it is possible that clinicians (within clinics) are another source of variation, an additional random effect for clinician within practices will be included if there is evidence of sufficient variability at this level. Multiple comparisons in testing the co-primary outcomes will be accounted for with an alpha = 0.025 to assess statistical significance. All other hypothesis tests will be two-sided with a significance level of 0.05.

Secondary outcomes (Table 1) will be analyzed using linear or logistic mixed effects regression, as appropriate. Similar random effects will be included accounting for the nested structure of the data. Secondary analysis results will be expressed as mean differences and regression coefficients or differences in proportion and odds ratios, as appropriate, with 95% confidence intervals (CIs).

Exploratory analyses will be conducted to test for potential effect modification by select patient characteristics. The effects of the health systems-level and hybrid interventions on antibiotic prescribing and parent satisfaction may differ based on race, ethnicity, insurance type, and clinical setting. Logistic mixed effects regression will be used including a main effect for the moderator and an interaction between the moderator and intervention variable. Due to the exploratory nature of these analyses, p-values will not be adjusted for multiple comparisons, however all subgroup analyses will be reported.

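### Clinics are randomised but the decision aid is issued by clinician, with no rule for clinicians who work in both arms, and Table 2 suggests (without proving) that Intermountain clinics share clinicians

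*Protocol article*

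**What the plan says.** - **Unit of randomisation** (Overview of study design): "Participating clinics will be randomly assigned to one of the two interventions (Fig. 1) using covariate-constrained randomization".
- **Unit that receives the differing component** (Clinician education): "Clinicians who practice in clinics randomized to the hybrid health systems-level plus shared decision-making intervention will also receive access to an electronic or paper" form of the aid, for AOM visits, with education on using it. Under Intervention components, both arms share the champion, record changes, feedback reports and learning sessions, so the aid and its education are the whole contrast. The aid exists as a webpage and will also be adapted for paper (Shared decision-making aid).
- **Model** (Statistical analysis): patients are nested in clinics, and "an additional random effect for clinician within practices will be included" if variability at that level warrants it. Feedback reports likewise compare each clinician with peers in one clinic.
- **Table 2**: "Clinics to be randomized 10 9 14" and "Total eligible clinics 45 33 31" (Alliance, Denver, Intermountain). The row "Clinicians per clinic (mean eligible clinicians, range") gives 20.3, 22.1 and 29.3. Clinician types are undetermined for Alliance, 123 (61.8%) and 43 (21.6%) for Denver, and 205 (71.9%) and 80 (28.1%) for Intermountain.

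The article does not say whether any clinician works at several clinics, and the limitations in its Discussion do not mention movement of clinicians between arms.

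**The concern.** Cluster randomisation protects the contrast only if the people who deliver the intervention stay within their cluster. Here a clinician who works at one hybrid and one control clinic is entitled to the aid and its training by the plan's own wording, while the children that clinician sees at the control clinic are analysed as controls. Training cannot be switched off by location, and a webpage can be opened anywhere.

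If this happens often enough, control children move towards the hybrid condition and both co-primary differences shrink. A null result could then mean that the aid adds nothing, or that it reached both arms. A clinician effect nested in clinic would also treat one person at two clinics as two unrelated people.

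The two adjacent Intermountain rows make this more than a hypothetical worry, because there are more clinician places than clinicians if the rows cover the same clinics.

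**Working it through.** **1. Clinicians against places (Table 2)**
- Intermountain clinicians: 205 + 80 = 285. Since 205/285 = 71.9% and 80/285 = 28.1%, 285 is the whole column.
- Places if 29.3 applies to the 14 clinics: 14 × 29.3 = 410; 410/285 = 1.44 clinics per clinician.
- Places if both rows cover all 31: 31 × 29.3 = 908; 908/285 = 3.19.
- Denver, same rows: 9 × 22.1 = 198.9, and 123/199 = 61.8%, 43/199 = 21.6%. The ratio is 1.00, so those rows share the randomised-clinic basis and show no overlap.
- Mixed basis at Intermountain (29.3 over 31 clinics, 285 in the 14): 285/14 = 20.4 per clinic, inside the stated range of 2 to 60. No sharing is needed.

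The figure of 1.44 is an average. The 410 − 285 = 125 extra places could come from 125 clinicians (44%) at two clinics each, or from as few as 10 who work at all 14 (125/13 = 9.6).

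**2. Chance that a shared clinician spans the arms**
Assume 7 of the 14 clinics per arm and no constraint on overlap. For a clinician at k clinics, P = 1 − 2·C(7,k)/C(14,k).
- k = 2: 7/13 = 54%.
- k = 3: 81%.

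**3. The plan's own sample size**
Inputs (Sample size and power): 1,566 children, 33 clinics, two-sided alpha 0.025, ICC 0.02, 12% antibiotic taken, 8-point difference.
- Mean cluster size 1,566/33 = 47.5; design effect 1 + 46.5 × 0.02 = 1.93; effective size per arm 783/1.93 = 406.
- Comparing 12% with 20% by the pooled two-proportion test gives power 81%, and 80% power needs 1,536 children, within 3% of 1,566. The stated figure is reproduced.

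**4. Effect of carry-over (assumed range)**
Let s be the share of Intermountain control-arm visits fully exposed to the aid, with children spread evenly over clinics. The control rate moves towards the hybrid rate by the fraction f = (14/33) × s.

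| s | f | Antibiotic difference (points) | Power | Satisfaction difference (points) | Power |
|---|---|---|---|---|---|
| 0 | 0 | 8.0 | 81% | 9.0 | 84% |
| 0.10 | 0.042 | 7.7 | 77% | 8.6 | 81% |
| 0.25 | 0.106 | 7.2 | 70% | 8.1 | 75% |
| 0.54 | 0.229 | 6.2 | 54% | 6.9 | 62% |

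All rows use ICC 0.02; satisfaction compares 76% with 85%. The last row is what step 2 gives if every Intermountain clinician worked at exactly two of the 14 clinics. If 44% did and the rest worked at one, s = (2 × 0.44/1.44) × 0.54 = 0.33.

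The stated antibiotic difference reproduces only upward from 12%, so the table uses that direction. For 12% against 4%, the same formula gives power of 98%, falling to 97%, 95% and 88% at the same three values of s. The proportional shrinkage f is the same in either direction.

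**The case against.** The strongest reply is that Table 2 is not a roster and mixes its bases.
- Intermountain's setting row is labelled as participating clinics but sums to 3 + 24 + 4 = 31.
- Denver's encounter mean is on the eligible-clinic basis (228 × 33 = 7,524, its patient total), although its clinician rows fit nine clinics.
- Denver's two clinician types sum to 166 of 199, whereas Intermountain's sum to 100%.
- The text speaks of over 200 clinicians, while Denver and Intermountain alone give 199 + 285 = 484.

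So the Denver check cannot show which basis Intermountain used, and the reading with 20.4 clinicians per clinic is open. This stands. A reader might infer from the counts that Intermountain clinicians each cover more than one clinic and that the contrast is therefore diluted. The documents support neither. Only an average exceeds one, only on a shared basis, and no section says that a clinician works in both arms or uses the aid at a control clinic.

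It also stands that the power figures rest on assumptions. The learning sessions are optional and the aid must be actively used, so carry-over may be partial. The full protocol may also hold a rule that a condensed article leaves out.

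What the reply does not remove is the stated access rule. It follows the clinician while allocation follows the clinic, so any clinician working in both arms is a route for carry-over.

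**Conclusion.** The concern holds as a contamination risk created by the stated access rule, with suggestive evidence of shared clinicians at one health system. It is not demonstrated dilution.

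The evidence is confined to Intermountain, which has 14 of the 33 clinics. Denver shows no overlap and Alliance cannot be checked. The averages of 1.4 to 3.2 clinics per clinician depend on the two rows sharing a basis.

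The loss of power from about 81% to between 77% and 54% is a conditional range. It depends on the assumed exposed share, full carry-over, an even spread of children over clinics, and the direction of difference that reproduces the plan's sample size. The direction of the bias is firmer: any carry-over of an effective aid moves both co-primary contrasts towards no difference. The point should be settled before clinics are randomised, because training cannot be withdrawn afterwards.

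**What to change.** 1. State which clinics the mean per clinic and the clinician-type counts in Table 2 cover.
2. Before randomising, extract the clinician-by-clinic roster. If no clinician is shared, the allocation and analysis can stay as they are.
3. If clinicians are shared, add a criterion to the covariate-constrained randomisation that minimises the share of AOM visits made by clinicians who would work in both arms, or keep clinics with heavy sharing in the same arm.
4. Record the clinician at the index visit, and fit any clinician effect as crossed with clinic rather than nested.
5. Pre-specify a sensitivity analysis that leaves out index visits to clinicians who are dual-arm on the baseline roster. Using the baseline roster keeps the exclusion independent of later behaviour.

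Restricting the aid to clinicians whose home clinic is hybrid is not recommended. It would withhold the aid from control-home clinicians seeing children at hybrid clinics, which could dilute the hybrid arm, and hybrid-home clinicians would still have it at control clinics.

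The cost is a roster extraction and one more constraint. The downside is fewer acceptable allocations and slightly looser balance on other covariates. No extra children or clinics are needed, and the article says recruitment has not begun.
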